## Abstract

Supplemental Digital Content is available in the text

## Introduction

1

Multiple sclerosis (MS) is a progressive inflammatory neurodegenerative disease characterized by a variety of disabling motor and non-motor symptoms.^[1]^ Motor symptoms such as muscle weakness and spasticity often lead to gait abnormalities and balance impairments.^[2]^ Non-motor symptoms such as cognitive dysfunction, depression, fatigue, and sleep disturbances are also common in these individuals.^[3]^ These symptoms together can result in a reduction in several quality of life (QOL) indices, including physical function, psychological well-being, self-care, work ability, interpersonal relationships, and reduced ability to perform daily activities.^[1,3,4]^

MS can be found all over the globe, with an estimated 2.3 million people diagnosed annually worldwide (33 cases per 100,000 people). The prevalence of MS is the highest in North America and Europe while Sub-Saharan Africa and East Asia have the lowest prevalence.^[5]^ In Jordan, data from 2004 to 2005 indicated a prevalence of 39/100,000 in the capital, Amman and 38/100,000 in the northern city of Irbid, which is considered a medium to high risk similar to western countries.^[6]^

Participation in physical therapy exercises (PTE) should start soon after the MS diagnosis, as research has shown that PTE delivers favorable outcomes in a variety of motor and non-motor symptoms in people with MS (PwMS), even in those who are not severely disabled.^[7–10]^ Balance, mobility, spasticity, fatigue, and overall QOL have been all found to improve from participating in PTE in the MS population.^[7–10]^ Unfortunately, the lack of awareness about the role of physical therapy in the management of PwMS might be the reason why PwMS do not receive adequate physical therapy services in Jordan.

Regenerative medicine using stem cell therapy injections has also proven its efficacy in numerous preclinical and some clinical studies in halting the neurodegenerative and neuro-inflammatory aspects of MS disease.^[11–13]^ One of the attractive stem cell therapy types is umbilical cord mesenchymal stem cells using Wharton Jelly (WJ-MSCs) due to their accessibility, high proliferation rate and their unique neuroregenerative potential as compared to bone marrow or adipose tissue derived MSCs.^[14]^ The WJ-MSCs was used in several studies for different aims such as cartilage repair and bone regeneration.^[14–16]^ The Cell Therapy Center (CTC) at University of Jordan has demonstrated the safety and efficacy of this therapy for the past years in the setting of clinical trials, the first of which was for PwMS who had not responded to any available pharmaceutical agent.^[11]^

While the effect of mesenchymal stem cell therapy on PwMS has been studied before,^[11]^ and PTE shown to be effective in PwMS,^[17]^ there is a limited evidence on the combined effect of WJ-MSCs and PTE on a wide range of symptoms in PwMS. Therefore, this study will be the first to assess the effect of a combined treatment intervention protocol (WJ-MSCs and PTE) that will eventually aid in a better understanding of the combined effect of 2 different treatment interventions versus when administered alone, in relation to motor and non-motor symptoms in PwMS. The findings of the study will emphasize the important role exercises have when added to regenerative medicine on managing common symptoms in PwMS. We also hope that the results of this study help guide clinicians and primary care givers on including physical therapy services soon after the diagnosis of MS to improve the QOL of these individuals.

### Objective

1.1

The purpose of this study is to explore the effect of PTE and WJ-MSCs injection versus PTE alone or WJ-MSCs alone on motor and non-motor symptoms in PwMS. We hypothesize that PwMS who receive the combined treatment of WJ-MSCs and PTE will demonstrate significant improvements on motor and non-motor symptoms compared to those who receive either WJ-MSCs alone or PTE alone.

### Trial design

1.2

The proposed study utilizes a randomized controlled design to examine the combined effect of a 6-month program on motor and non-motor symptoms in PwMS. This study is single-blinded where the researchers involved in the assessments are blinded to the allocation of the participants to each group. We aim to recruit 60 participants with MS (20 in each group) that will be randomly allocated to 1 of 3 groups using a computer-generated software to either a combined treatment group (PTE + WJ-MSCs), PTE alone control group or WJ-MSCs alone control group after going through a battery of comprehensive assessments (Fig. 1).

**Figure 1 F1:**
[figure not shown]
Flow chart demonstrating the study procedures from screening through study completion.

## Methods

2

### Study setting and recruitment

2.1

Participants will be recruited from the MS registry list at the CTC facility at University of Jordan, from personal referral from consented participants, area physicians, or study personnel, and advertisement on social media.

### Eligibility criteria

2.2

Interested participants will be checked for the inclusion/exclusion criteria where they will undergo a thorough neurological exam performed by a neurologist to generate the expanded disability status scale (EDSS), and a trained research personnel will perform the mini mental state examination.^[18]^ A screening form is also filled out for every participant that includes demographics, general history of the disease, past, and current medication intake and relevant clinical aspects of the disease. Participants will be selected based on the following eligibility criteria:

Inclusion criteria:

(1)Males and females.(2)Eighteen years and older.(3)Written informed consent prior participation.(4)Independent in ambulation even with the use of an assistive device.(5)All types of MS.(6)EDSS score < 6.5.(7)mini mental state examination score ≥ 24.

Exclusion criteria:

(1)Uncorrected vision loss.(2)History of a nervous system disorder other than MS.(3)Severe physical, neurological, or sensory impairments that would interfere significantly with testing.(4)Developmental history of learning disability or attention-deficit/hyperactivity disorder.(5)Relapse and/or corticosteroid use within 4 weeks of assessment.(6)Acute ischemic cardiovascular event or coronary artery bypass surgery less than 3 months.(7)Uncontrolled blood pressure with medication (blood pressure (BP) > 190/110 mm Hg).

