##### Aerobic exercise

2.3.2.3

The following guidelines are followed across the 2 stages: exercise intensity in stage I is 50% to 59% of heart rate reserve for 3 months; increased to stage II 60% to 69% of heart rate reserve for remaining 3 months. Exercise session total time is 40 minutes on the recumbent stepper supervised by the PT including 5 minutes warm up, 30 minutes aerobic training, and 5 minutes’ cool down. Aerobic exercise is performed on the same recumbent stepper used for the submaximal testing during the baseline assessment (Model SCIFIT-StepOne). The handles and seat is adjusted according to the participant's arm and leg length prior to the exercise session (taken from the submaximal test performed at baseline). Pre and post exercise vital signs (HR and BP) are taken. Heart rate is monitored during the exercise using polar heart rate monitors. Five minutes’ warm-up and cool down on the recumbent stepper is set at 25 watts load at a comfortable pace. Exercise intensity during the 30 minutes’ period is increased to the prescribed target heart rate range that is initially calculated using the Karvonen formula.^[23]^ Intensity is adjusted according to physiologic response but not to exceed the target heart rate range during the 30 minutes’ period. Rate of perceived exertion is monitored before and after the aerobic training period using the Borg scale. During the 30 minutes of exercise, each participant is instructed to keep their stepping pace at 100 steps/min that would be visible for them on the machine monitor. However, each participant is allowed ± 5 steps (95–105 steps/min) during the exercise. The intensity used, vital signs, rate of perceived exertion, and any comments or changes during the session is recorded on a weekly exercise log. After the cool down, participants are allowed ample time to rest before they leave.^[24]^

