#### Motor assessment measures

2.4.1

*2.4.1.1. Aerobic fitness* is assessed using the submaximal testing. In this test a seated recumbent stepper (Model SCIFIT-StepOne) will be used, which provides simultaneous movement of the upper and lower extremities in a continuous stepping motion. During the submaximal exercise test, the participants are asked to move their arms and legs in an alternating pattern at a constant speed of 100 steps per minute and resistance (Watts) will be increased every 3 minutes according to the total body recumbent stepper submaximal exercise test until 85% of age-predicted heart rate max is met or participant can no longer continue due to fatigue (test termination endpoint). During the test, heart rate is monitored using polar heart rate monitors. Ten seconds prior to the end of every stage, heart rate is taken and recorded. Once the test is finished, the participant will continue to step at a comfortable self-selected speed with minimal resistance for 2 minutes or until heart rate returns to near baseline levels.^[27]^ The outcome measure is predicted VO2 max calculated by a formula using the participant age, sex, weight, watts used, and HR.^[27]^

*2.4.1.2. Balance and mobility* are assessed using the following assessment tools:

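### The only blood-pressure exclusion is worded to reach treated candidates only, so an untreated candidate above the same limit stays eligible for the exercise test and training

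*Protocol article*

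**What the plan says.** All references are to the Protocol article.

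- **Section 2.2, exclusion 7**, is the only eligibility criterion on blood pressure: "Uncontrolled blood pressure with medication (blood pressure (BP) > 190/110 mm Hg".
- **The two nearest other exclusions** are number 6, "Acute ischemic cardiovascular event or coronary artery bypass surgery less than 3 months", and number 3, "Severe physical, neurological, or sensory impairments that would interfere significantly with testing".
- **Screening steps in section 2.2** are a neurological examination, a cognitive test and a form that covers demographics, disease history and "past, and current medication intake and relevant clinical aspects of the disease". A blood-pressure reading is not listed among them.
- **Section 2.4.1.1** describes the submaximal stepper test. In it "resistance (Watts) will be increased every 3 minutes", and it runs "until 85% of age-predicted heart rate max is met or participant can no longer continue due to fatigue". Heart rate is monitored throughout; blood pressure is not mentioned.
- **Section 2.5** gives the assessment battery to every eligible participant at baseline and again at 3, 6 and 12 months. **Section 1.2** places random allocation after the baseline battery.
- **Section 2.3.2.3** sets training at 50% to 59% of heart rate reserve for three months, then "increased to stage II 60% to 69% of heart rate reserve for remaining 3 months". This applies to the exercise-alone and combined arms.
- **Sections 2.3.2 and 2.3.2.3** have blood pressure taken before and after each supervised session. **Section 2.3.1** has vital signs measured before each stem-cell treatment. None of these sections states a limit or a consequence.

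**The concern.** An eligibility criterion is applied from its text. Exclusion 7 has two parts: a condition (pressure uncontrolled despite medication) and a number in brackets. The condition decides whom the number applies to. As worded, two candidates with identical readings above the limit are treated differently: the one on medication is excluded and the one without is not.

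What is at stake is participant safety and consistent screening. The criterion is the only stated blood-pressure gate before a graded exercise test that ends on heart rate or fatigue, and the only one with a limit before six months of supervised aerobic exercise. Candidates whose high pressure has never been treated would pass it.

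**Working it through.** There is no figure of the plan to reproduce and no sample-size, power or error-rate calculation involved. The check is a literal reading of the criteria followed by tracing the participant's path.

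**Step 1. Does another criterion close the gap?** Going through section 2.2:

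| Criterion | Subject | Excludes untreated high pressure? |
|---|---|---|
| Inclusions 1 to 7 | sex, age, consent, ambulation, MS type, EDSS, cognitive score | No |
| Exclusions 1, 2, 4 | vision, other nervous system disorder, developmental history | No |
| Exclusion 3 | impairments that interfere with testing | Not named; high pressure need not interfere with testing |
| Exclusion 5 | recent relapse or corticosteroid use | No |
| Exclusion 6 | recent ischaemic event or bypass surgery | No |
| Exclusion 7 | pressure above 190/110 mm Hg, tied to medication | Not on the literal wording |

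**Step 2. Apply exclusion 7 to example candidates** (the first two differ only in treatment).

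- On medication, both values above the limit: excluded.
- Not on medication, both values above the limit: not excluded by number 7 or, from step 1, by any other criterion.
- On medication, one value above the limit (195/100, as an illustration): excluded if either value is enough, eligible if both are needed. The text does not say. This is a separate, lesser question of detail and has no bearing on the untreated candidate.

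**Step 3. Follow the untreated candidate through the trial.**

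1. Screening (2.2): medication is recorded; no blood-pressure reading is listed.
2. Baseline battery (2.5, 2.4.1.1): the stepper test is taken by all 3 × 20 = 60 planned participants. Its stated end points contain no blood-pressure criterion.
3. Allocation (1.2): follows the battery.
4. Training (2.3.2, 2.3.2.3): given in two of the three arms, 2 × 20 = 40 participants. Pressure is measured, but no limit or action is given.
5. Injections (2.3.1): vital signs are measured, again without a limit or action.

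The 60 and 40 are the numbers planned for the test and the training. They are not estimates of how many people the wording would let through.

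**The case against.** **The wording allows another reading.** The phrase could mean pressure that medication has not brought under control, with the bracket simply defining uncontrolled, and the authors may have meant the limit for everyone. A screener might well apply it that way. This is a fair point about intent, so the defect is one of drafting; a reader might infer that people above the limit will be enrolled, and the documents do not show that. But even this reading presupposes medication, so it does not bring an untreated candidate within the criterion.

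**The article condenses a fuller protocol.** Who is measured at screening and how a pair of values is read may be set out there or on the screening form. This disposes of the pair as a finding in its own right. It does not dispose of the medication qualifier, because the article does state that criterion, and states it too narrowly.

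**There are later checks.** Sessions are supervised by a physical therapist, pressure is taken before and after exercise, and intensity is adjusted to physiologic response. These reduce the practical risk during training. They come after the baseline test, and no blood-pressure limit is attached to them.

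**A stronger inference: unequal loss between arms.** A reader might infer that unsuitable people would drop out mainly from the two exercise arms and bias the comparison with stem cells alone. The documents do not support this. The baseline test precedes allocation, so a problem found there cannot unbalance the arms. All arms repeat the assessments, vital signs are also taken before injections, and no blood-pressure withdrawal rule is stated.

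**Conclusion.** The point holds as an under-inclusive eligibility rule. On its literal wording, exclusion 7 does not reach an untreated candidate above the sponsor's own limit, and no other listed criterion does so before the baseline stepper test or before training in two of three arms.

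Its size cannot be put as a number of people. Counting possible combinations of treatment status and systolic or diastolic excess would only count logical cases and say nothing about frequency, so no such figure is offered. No estimate, error rate or comparison between arms is shown to be affected.

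The conclusion rests on two assumptions: that screeners apply the criterion as worded, and that it is there at least partly because participants will exercise. The protocol does not state its purpose.

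**What to change.** The sponsor should reconcile exclusion 7 in section 2.2 with the exercise test and training in sections 2.4.1.1 and 2.3.2.3, so that its own existing limit is not conditional on medication use. It should also confirm that blood pressure is checked at screening, since section 2.2 lists no such step. While making the edit, it can say whether one value or both must exceed the limit. No threshold, treatment or other clinical rule is proposed here; those remain the sponsor's to set.

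The cost is one line in the eligibility list, one reading at screening, and possibly some candidates not enrolled, in a number the documents do not give. A change to the protocol needs the ethics board's approval under section 2.10.

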### Interventions

2.3

#### Mesenchymal stem cells (control group 1)

2.3.1

The stem cell treatment protocol for all participants in the WJ-MSCs only group or the combined group consists of using cryopreserved allogenic WJ-MSCs donor. The WJ-MSCs group receive 3 injections. The first one contains 100x10^6^ cells intrathecally and 50 x10^6^ cells intravenously. After 1 month, the second injection is administered with the same content as the first injection. The third intrathecal injection contains 8 to 10 mL of the WJ-MSCs’ conditioned media after 3 months of the first injection. The WJ-MSCs is administered by an internal medicine specialist or the neurologist himself. Prior to the intrathecal injection, the same volume of MSCs injected is withdrawn as cerebrospinal fluid (CSF) in order to maintain the CNS pressure and decrease the post-intrathecal injection headache.

Prior to each treatment, patients’ vital signs are measured at the CTC “ICU equipped” transplantation room. The participants are kept under observation for an hour post injection for any immediate adverse events. Any related adverse event is noted by the CTC nurse, 24 hours, 1 week, and 1 month post treatment through direct communication with the participant.

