#### Physical therapy exercise) program (control group 2)

2.3.2

The PTE program utilized in this study is partly based on 2 previous published exercise programs that were found to be effective in improving balance and mobility in PwMS.^[7,21]^ Following the physical activity guidelines for adults with MS,^[22]^ we will further add 30 minutes of aerobic exercise to the program. Additionally, we will also follow the guidelines of having a minimum 2 sessions per week of physical activity for PwMS. The PTE program consists of a mixed program including the following types of exercises: balance, resistance, flexibility, and aerobic exercises performed 2 times per week for a total of 6 months. The intensity of the exercise will be progressed throughout the 6 months’ period and consists of 3 stages of progression for the resistance/flexibility and balance programs, and 2 stages of progression for the aerobic exercise program. Participants will be progressed to each stage depending on their tolerance and performance level of the exercises. Each session will take 60 to 80 minutes to finish, and will be supervised by a trained physical therapist (PT). Exercise will be performed in a well-equipped lab space at the CTC at University of Jordan. Following the 6 months supervised program, participants will continue the remaining 6 months of the study period performing a home exercise program (HEP).

The PTE session is divided as the following: pre-exercise vital signs measured using a digital HR/BP monitor, 5-minute warm-up exercises, 10 to 15 minutes of strength and flexibility exercises, 10 to 15 minutes of postural balance exercises, 40 minutes of aerobic exercise on a recumbent stepper machine and a 5-minute cool-down. Vital signs will be taken again post-exercise. Resting periods will be given to each participant before progressing to other forms of exercises and as necessary to decrease levels of fatigue. Participants will be allowed to choose the appropriate days/times to do the sessions upon their convenience but will be encouraged to choose the session every other day to allow a day rest in between. Vital signs, comments, and progress of each session will be documented for every participant using weekly exercise logs.

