### Participant timeline

2.5

Eligible participants will be scheduled for their baseline assessments. They will undergo a comprehensive battery of measures including motor, non-motor, and medical assessments, which will take around 2 to 3 hours to complete. Part of the baseline assessment that include MRI imaging will be performed on another day within a week from the baseline assessment on a time convenient to the participant. Participants will repeat these measures at 3, 6, and 12 months post the baseline assessment (Fig. 1).

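### The one stated adverse-event procedure records related events after the first hour, ends about month 4 of 12, and is tied to injections, so it cannot run in the exercise-alone arm

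*Protocol article*

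**What the plan says.** Section 2.3.1 of the protocol article applies to two of the three arms: "The stem cell treatment protocol for all participants in the WJ-MSCs only group or the combined group". It sets two layers of safety collection.

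- Just after the injection: "The participants are kept under observation for an hour post injection for any immediate adverse events". This layer has no relatedness condition.
- After that hour: "Any related adverse event is noted by the CTC nurse, 24 hours, 1 week, and 1 month post treatment through direct communication with the participant". This layer is limited to related events and to three time points. The section does not say who decides that an event is related, or how.

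The injection schedule is in the same section: "The WJ-MSCs group receive 3 injections"; "After 1 month, the second injection is administered with the same content as the first injection"; and the third injection, of "conditioned media after 3 months of the first injection".

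The other contacts are described without an adverse-event item. For the exercise programme (section 2.3.2): "Vital signs, comments, and progress of each session will be documented for every participant using weekly exercise logs". In the home phase (section 2.3.2.4), a therapist telephones monthly about compliance and barriers to exercise. For all arms (section 2.5): "Participants will repeat these measures at 3, 6, and 12 months post the baseline assessment". The measures meant are the motor, non-motor and medical batteries of section 2.4, which name no adverse-event or relapse enquiry.

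**The concern.** Two features of the written rule matter, and a third follows from them.

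1. **Causality is screened before recording.** An event judged unrelated at the time leaves no record. Relatedness is a judgement, and it often changes once events are seen together across participants. That second look is impossible for events never written down.
2. **The schedule ends with the injections.** Follow-up lasts a year, but the stated enquiries stop one month after the third injection.
3. **The trigger exists in two arms only.** The trial compares the combined treatment with each component alone. If harms are sought in different ways and at different times in the arms, a difference in event counts may reflect the collection rule and not the treatment.

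Unlike a gap in the analysis methods, this cannot be repaired later, because a subsequent analysis plan cannot recover unrecorded events. It also touches efficacy. The eligibility criteria exclude people with a relapse or corticosteroid use within 4 weeks of assessment, so the protocol accepts that these disturb the measurements. Yet the article states no capture of either during follow-up.

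**Working it through.** The plan gives no figure on this point to reproduce. The check is a calendar count from its own schedule.

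**Inputs**
- Injections at months 0, 1 and 3 (section 2.3.1).
- Contacts at 24 hours, 1 week and 1 month after treatment (section 2.3.1). I read this as after each injection, because the same section uses *each treatment* for each injection when it describes vital signs.
- Follow-up of 12 months (section 2.5).
- 60 participants, 20 per arm, 2 arms receiving cells (sections 1.2 and 2.3.1).

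**Contacts per injected participant:** 3 injections × 3 contacts = 9.

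**Stated contacts per exercise-alone participant:** 0, since there is no injection to trigger them. This counts what the article states, and not necessarily what will be done.

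**Last stated contact:** month 3 + 1 = month 4. Time remaining: 12 − 4 = 8 months, and 8/12 = 67%.

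**Time inside a one-month window:** months 0–1, 1–2 and 3–4, which is 3 months. Outside: 12 − 3 = 9 months, and 9/12 = 75%. The 67% is the more cautious figure, because it ignores the gap between months 2 and 3.

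**Whole trial:** injected participants contribute 40 × 3 = 120 person-months inside a window, out of 60 × 12 = 720 planned. 120/720 = 16.7%.

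**Sensitivity to the reading:** if *post treatment* meant only after the full course, there would be 3 contacts instead of 9. The last would still be at about month 4, with 8 months left.

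**Other contacts beside the rule**

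| Contact | Arms | Stated adverse-event enquiry |
|---|---|---|
| First hour after injection | Both cell arms | Yes, any immediate event |
| 24 hours, 1 week, 1 month after injection | Both cell arms | Yes, related events |
| Supervised sessions to month 6 | Both exercise arms | No; vital signs, comments, progress |
| Monthly calls, months 6–12 | Both exercise arms | No; compliance and barriers |
| Visits at 3, 6 and 12 months | All | No; motor, non-motor and medical measures |

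The last row is the only contact common to all three arms. After month 4 it is also the only stated contact in the cells-alone arm, at months 6 and 12.

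**The case against.** The strongest reply is that this is a condensed article. Section 2.3.1 describes nursing follow-up after an invasive procedure and does not claim to be the trial's whole safety system. General event forms and serious-event reporting usually sit in the full protocol, which is not shown. Closer monitoring after an intrathecal injection is an ordinary choice, the objective concerns symptoms, and section 2.9 declares no between-arm safety comparison.

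Much of that stands, and it rules out several stronger readings that a reader might infer.

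- *Events are noted only if related.* Not so in the first hour, when any immediate event is observed. The restriction applies afterwards.
- *Unblinded staff filter the events.* The article does not say so. It names a nurse as recording events, but not who judges relatedness. Its blinding statement covers assessors and is silent on the nurse.
- *Most of the year has no safety contact.* Too broad. All arms have visits that include disability scoring, laboratory markers and MRI. Exercisers also have supervised sessions with vital signs, then monthly calls. What is missing is a stated adverse-event question at those contacts.
- *The exercise-alone arm has no adverse-event collection.* The article is silent on this, and silence is not proof of absence.
- *Relapses and injuries would be missed.* They might be noticed through disability scores or by the supervising therapist. But seeing a consequence is not the same as recording an event.

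What the reply does not remove is the explicit text. The relatedness condition, the injection-linked schedule and its end at about month 4 are written down. The lack of a declared safety comparison lowers the severity, but readers weighing what each component adds will still set harms side by side.

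**Conclusion.** The point holds for what the article states. After the first post-injection hour, the only procedure it describes screens events on causality before recording. It gives 9 contacts per injected participant and ends at about month 4, with 8 of 12 months (67%) remaining. It cannot operate in the exercise-alone arm. On this wording, event counts would not be comparable between arms, and late events in the cell arms have no stated capture.

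The figures assume injections on schedule, full follow-up, and a first injection close to baseline; a delay would move the last contact by the same amount. The part about the exercise-alone arm and the later visits depends on there being no general procedure in a fuller protocol. If there is one, section 2.3.1 needs only its wording corrected. No declared analysis is invalidated, so this should be fixed as a cheap improvement and is not a fatal flaw.

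**What to change.** - Delete *related* as a condition for recording in section 2.3.1.
- Record all adverse events, serious events, relapses and steroid courses, whatever the cause, on one standard form in all three arms at the existing 3-, 6- and 12-month visits. Optionally add a short call at month 1, or put the same questions into the planned monthly calls. Those calls reach exercisers only, so extending them to the cells-alone arm would be needed for them to count in a comparison.
- Assess relatedness afterwards, in a separate field, and state who does it.
- Keep the post-injection contacts as additional collection, reported separately.
- Base any between-arm comparison on the common schedule only.

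The cost is one extra form at visits already planned and, if the options are taken up, a few short telephone calls.
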